### Data management

The evaluation data will be derived from a pre-set spreadsheet with varied baseline attributes. The research data will be stored in a safe database. Hard copies of evaluation forms, signed informed consent forms, and other non-electronic documents will be safely preserved in the study setting. Every month until the trial is over, a complete backup of the data entries will be performed. The lead investigators will supervise the data gathering and reporting processes. The accuracy of the research papers must be properly reviewed. At the end of the study, the Excel spreadsheet will be published and delivered to the statistician for the necessary analysis. A checklist can be used to avoid data loss due to ineffective staff processes. Due to the thorough follow-up assessment of this trial, participant retention and completion of follow-up assessments are anticipated to be quite high. The patients in this trial will be invited to follow-up exams after six weeks.

### Statistical analysis

Samples taken in accordance with the protocol and recorded on a basis that includes all relevant characteristics. Dataset of outcome variables including demographic, physical, laboratory and vitals information will be collected and tabulated in Excel, and will be analysed using R-Software version 4.3. Demographic variables such as age and gender and physical examination (height, weight, BMI), laboratory parameters (haemoglobin, Erythrocyte Sedimentation Rate (ESR), Liver Function Test (LFT), Kidney Function Test (KFT)), and vitals (respiratory rate, pulse rate, systolic blood pressure, diastolic blood pressure and SpO
_2_ levels) will be collected. Outcome variables such as BBS, DGI, TIS, 10MWT, FRT and FES will be presented over descriptive statistics with categorical tabulation for frequency and percentage, while quantitative measurements with minimum, maximum, mean and standard deviation.

The primary outcome variables will include the BBS for measuring balance and the DGI for measuring gait outcome variables, the secondary outcome variables include the TIS, FRT, 10MWT and FES. Variables as primary and secondary parameters for their measuring assessment at different time visits will be assessed to find the significance in mean at 5% level of significance at P-value < 0.05. Statistical analysis will be performed for hypothesis testing for paired pre and post analysis using a paired t-test for normal data or non-parametric test such as Wilcoxon signed-rank test for non-normal data. Similarly, an unpaired t-test will be used for two independent groups for the change in parameters readings of primary and secondary variables at two different visits.

Data over the outcome variables will be analysed for normality (normal distribution) using Kolmogorov–Smirnov test. If data results over non normal distribution then alternate non parametric test will be used.

Confounding variables will be analysed with generalised linear model to find the random and fixed effects over the outcome variables. Association analysis for finding significance of cofounding parameters will be examined by using Chi-squared test or Fisher’s exact test or by using multi-variant analysis.

Full analysis set for the values of outcome variables will be analysed for the results missing data will be covered with imputation method by calculating the mean and median over the existing data.

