**Conclusions:**

There is sufficient evidence to derive the conclusion that the functional mobility and balance of stroke victims can be improved with physiotherapy. Therefore, this study will try to seek the comparison of mCIMT (group A) and MRP (group B) in sub-acute stroke subjects and compare the two regimes to determine which one will be superior.

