### Trial design

A single-centre, two arm, parallel group, comparative open labelled superiority trial will be conducted.

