### Outcome measures

Time frames at baseline and six weeks later.

*Primary outcomes*
1.
Change in Berg Balance Scale (BBS)
The BBS is a scale with 14 items that is frequently used and is a standardized balance assessment that uses observation to quantitatively assess a patient’s capacity for balance, either statically or while engaging in a variety of planned routine daily tasks. For evaluating static and dynamic balance following a stroke, The inter-rater and intra-rater reliability of BBS for the patients with stroke is 0.97 and 0.98, respectively.
^
15
^ Each item on the scale will be given a score between 0 and 4, giving the patient an overall ranking of 56. A score of 0 means you didn’t complete the project, and a score of 4 means you did it independently.
^
16
^
2.
Change in Dynamic Gait Index (DGI)
The goal of the DGI is to examine dynamic balance while in motion. Eight of the tasks ask participants to keep their balance when walking normally and while doing so in various conditions (such as adjusting their speed, turning their heads to go around obstacles, pivoting around and climbing steps). Each item is given a score between 0 and 3 points, with a maximum score of 24. A higher DGI score indicates greater independent functional mobility. The DGI has been shown to yield ratios of subject variability to total variability with excellent interrater reliability 0.96 and test-retest reliability 0.98.
^
17
^

*Secondary outcomes*
1.
Change in Trunk Impairment Scale (TIS)
The TIS assesses post-stroke trunk movement, static and dynamic sitting balance, and trunk movement coordination. The TIS is used to analyse motor dysfunction of the trunk after a stroke, static and dynamic seated balance and coordination of trunk movement. Overall reliability for clinical care and research in the TIS, 0.96.
^
18
^
2.
Change in Functional Reach Test (FRT)
Utilising a yardstick fastened to the wall at the acromion’s height, functional reach is determined. Functional reach has been shown to exhibit test-retest reliability, interobserver consistency, criterion validity, and concurrent concept validity in earlier investigations. Additionally, it has been demonstrated that in patients undergoing rehabilitation, functional reach is sensitive to clinically significant changes in balance.
^
19
^
3.
Change in 10 Meter Walk Test (10MWT)

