### Sample size calculation

We estimated the sample size using a power analysis with 80% power and 5% Type 1 error for the main variables. The BBS score, in comparison to the difference in mean score pre and post treatment for mCIMT group from baseline to end visits. For the study, we used the previously determined effect size difference in percentage from the RCT.
^
22
^ Formula using mean difference:

$$n1=n2=2\frac{{\left(Z_{\alpha }+Z_{\beta }\right)}^{2}\sigma^{2}}{{\left(\delta \right)}^{2}}$$
Primary Variable (BBS)

Mean ± SD (Pre) result on BBS for mCIMT = 48.8 ± 4.7

Mean ± SD (Post) result on BBS for mCIMT = 52.5 ± 3.5

Difference = 3.7

Pooled std. dev. = (4.7 + 3.5)/2 = 4.1

$$\text{N1}=2^{*}\left[{\left(1.64+0.84\right)}^{2}{\left(4.1\right)}^{2}\right]/{\left(3.7\right)}^{2}=15$$

Considering 10% dropout = 2

Total samples required = 15 + 2 = 17 per group.

Total sample size required = 15

Notations:

$$Z_{\alpha }=\text{1.64 bat 5\% l.o.s. at both sides total 10\% type I error}$$

α=Type I error at 5%

$Z_{\beta }=0.84\;\left(1-\beta \right)=\text{Power at}\;80\%$

σ=std.dev=0.5pooledstd.dev

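### Two primary outcomes (BBS and DGI) are each tested at an unadjusted 5% with no rule on which of them decides superiority, and only BBS is sized

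*Protocol article*

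**What the plan says.** The Outcome measures section lists two primary outcomes, change in BBS and change in DGI, and four secondary ones (TIS, FRT, 10MWT, FES). The Statistical analysis section repeats this: "The primary outcome variables will include the BBS for measuring balance and the DGI for measuring gait outcome variables".

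One significance rule covers primary and secondary variables alike; they "will be assessed to find the significance in mean at 5% level of significance at P-value < 0.05". For the comparison of arms, "an unpaired t-test will be used for two independent groups for the change in parameters readings of primary and secondary variables".

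The claim to be made is one of superiority, in whichever direction it falls. Trial design: "A single-centre, two arm, parallel group, comparative open labelled superiority trial will be conducted". The abstract's Conclusions say the trial will "compare the two regimes to determine which one will be superior".

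The Sample size calculation states 80% power and 5% type I error for the main variables (plural), then names BBS as its one primary variable and computes from BBS figures only. No effect size or SD is given for DGI. The notation in that section describes its z value of 1.64 as 5% on each side, 10% in total.

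**The concern.** A superiority trial needs a rule, set in advance, that turns its primary results into a verdict. Here there are two primary results, each tested at the full 5%, and no such rule. The document could be read as needing a win on BBS, on DGI, on either or on both, and these readings have different error rates. Under the either-wins reading, the 5% type I error stated for the main variables does not hold for the trial's conclusion.

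Two features make the gap matter here. Both arms are active and either may be named superior, so a result that favours one programme on balance and the other on gait has no agreed interpretation. The trial is also open label with no blinding (Methods, Protocol), so nothing in the plan prevents the decisive outcome from being chosen once results are known.

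The power claim has a related fault. It is worded for more than one variable, but only BBS supports it.

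**Working it through.** **Inputs.** From the Statistical analysis section: two primary outcomes, and P < 0.05 for each. From the Sample size calculation: difference 3.7, SD 4.1, z values 1.64 and 0.84, 10% dropout, 15 per group before dropout and 17 after. Assumed here: the tests are two-sided, because either programme may win, and the two test statistics are correlated 0 to 0.95, because the document gives no value.

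**1. The plan's own sample size.** n = 2(1.64 + 0.84)² × 4.1² / 3.7² = 2 × 6.1504 × 16.81 / 13.69 = 15.1 per group. The document gives 15, and 17 after dropout. The figure is reproduced (strict rounding up would give 16). It uses BBS alone.

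**2. Error if either outcome can carry the claim.** Neither programme is better in truth, and each test is at two-sided 5%.

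- Bound under any dependence: 0.05 + 0.05 = 10%.
- Independent tests: 1 − 0.95² = 9.75%.
- Correlated tests: 1 − P(|Z₁| < 1.96 and |Z₂| < 1.96), with (Z₁, Z₂) bivariate normal:

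| Assumed correlation | Chance of at least one false positive | Ratio to 5% |
|---|---|---|
| 0 | 9.75% | 1.95 |
| 0.3 | 9.5% | 1.9 |
| 0.5 | 9.1% | 1.8 |
| 0.7 | 8.3% | 1.7 |
| 0.8 | 7.8% | 1.6 |
| 0.9 | 7.0% | 1.4 |
| 0.95 | 6.5% | 1.3 |

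Simulated t-tests with 15 per arm agree: 9.8%, 9.0%, 8.3% and 7.8% at correlations 0, 0.5, 0.7 and 0.8.

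**3. Error under other rules.** If both outcomes must be significant, the error is at most 5%. If BBS alone decides, or DGI is tested only after BBS succeeds, it is also at most 5%. The inflation therefore belongs to the either-wins rule only.

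**4. Power on the plan's BBS inputs at the level the analysis uses.** With 15 evaluable per group, the standardised effect is 3.7 / (4.1 × √(2/15)) = 2.47.

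- At z = 1.64 (one-sided 5%, or two-sided 10%): Φ(2.47 − 1.64) ≈ 80%.
- At z = 1.96 (two-sided 5%): Φ(2.47 − 1.96) ≈ 70%.
- At z = 2.24 (two-sided 2.5%, an equal split between two outcomes): Φ(2.47 − 2.24) ≈ 59%.

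The matching sizes for 80% power are 20 per group at two-sided 5% (2 × 2.80² × 16.81 / 13.69 = 19.3; 23 with 10% dropout) and 24 per group at two-sided 2.5% (27 with dropout).

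These figures take 3.7 at face value. The section describes it as a before–after change within the mCIMT group of an earlier trial, not a difference between arms. No corresponding calculation is possible for DGI, because the document gives no inputs.

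**The case against.** The strongest reply is that the protocol never says a win on either outcome is enough. The third objective compares the programmes on balance and gait together, which is compatible with requiring both. It is also compatible with two separate claims, one on balance and one on gait, where the need for adjustment is debated. Under a both-must-win rule there is no inflation. This stands: the inflation is conditional, and the firm finding is that the rule is missing.

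A reader might infer that the false-positive rate is nearly doubled. That fits only independence or weak correlation. Outcome measures describes the DGI as examining balance during movement, and the BBS covers dynamic balance too, so positive correlation is plausible; at 0.5–0.8 the ratio is about 1.8 to 1.6.

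A reader might also count all six outcomes and reach 1 − 0.95⁶ = 26%. That needs six independent outcomes and a rule letting any of them decide superiority. The outcomes are closely related (with a common correlation of 0.5 or 0.7 the figure is about 21% or 16%), four are labelled secondary, and nothing lets them decide.

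A contradictory split, with both outcomes significant in opposite directions, is very unlikely by chance alone: about 0.1% at independence. It could arise from real opposing effects, so it deserves a pre-set reading, but it is a small part of the point.

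Finally, a separate analysis plan may hold a multiplicity rule. Silence here would not be a finding. But the protocol is not silent: it fixes two primaries, sets an unadjusted 5% for each, and states error and power properties for the main variables together.

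**Conclusion.** The concern holds in a conditional form. The protocol names two primary outcomes, tests each at an unadjusted 5%, and does not say how they combine into a verdict of superiority. If either can carry the claim, the type I error for the conclusion is above the stated 5% at every correlation considered: at most about 10%, and about 8–9% at correlations of 0.5–0.8. This rests on two-sided tests, an either-wins reading that the document leaves open, and correlations that are assumed.

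The power statement is unsupported for DGI at any level. For BBS it holds only at the z = 1.64 used, which is 10% two-sided; at two-sided 5% it is about 70% with 15 evaluable per group, on the document's own inputs.

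This should be corrected before enrolment. It does not invalidate the design.

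**What to change.** State the decision rule before the first participant is enrolled. One that keeps 5% and matches the variable used for sizing is:

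1. Test the between-arm difference in change in BBS first, at two-sided 5%.
2. Test the between-arm difference in change in DGI at two-sided 5% for a confirmatory claim only if BBS is significant.
3. Report TIS, FRT, 10MWT and FES as supportive estimates with 95% confidence intervals that do not decide superiority.
4. Restrict the power statement to BBS, and restate it for the two-sided 5% test: about 70% with 15 evaluable per group on the present inputs, or 20 evaluable per group (23 with 10% dropout) if 80% is to be kept.

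Requiring both outcomes to be significant would also hold 5% without splitting alpha, but it needs a power calculation for DGI that the document cannot supply. An equal split would need 24 per group for BBS.

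**Cost.** The decision rule itself needs no extra participants, and Study status says the trial has yet to begin. It is more than a wording change, though. It gives DGI a lower rank among the primary outcomes, ethics approval and registration are in place, and the Protocol amendments section says no further changes could be made. A protocol and registry amendment is needed. The statistical price is that there is no confirmatory claim on gait if BBS is not significant.

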### Aims and objectives

1.To study the effect of mCIMT in addition to conventional therapy on balance (using the Berg Balance Scale (BBS)) and gait (using the Dynamic Gait Index (DGI)) in sub-acute hemiplegic stroke.2.To study the effectiveness of MRP along with conventional therapy on balance (BBS) and gait (DGI) in sub-acute hemiplegic stroke.3.To compare mCIMT and the MRP in improving balance and gait in sub-acute hemiplegic stroke patients along with conventional therapy.

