### Inclusion criteria

Patients will be included if they fulfil the following inclusion criteria: i) Sub-acute stroke in both men and women between the ages of 45 and 65 years; ii) Mini-Mental State Examination score ≥24; iii) Modified Rankin Scale ≤3; iv) patients with Brunnstrom stage for hand and leg ≥4; v) Modified Ashworth Scale ≤2; and vi) be able to comprehend and adhere to instructions.

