### Interventions

*Criteria for discontinuing allocated interventions for a given trial participant*

If any patients in any of the allocated groups develop any complication (
*e.g.*, deep venous thrombosis), their participation will be discontinued in the study. The patients will then receive appropriate care and offered outpatient rehabilitation as needed. Study participants will be retained in the trial (unless they withdraw their consent) to enable follow-up data collection and to prevent missing data.

*Adherence and concomitant care*

During the first consultation, the importance of following the study guidelines and adhering to the allocated group will be highlighted. Exercise adherence will be recorded as a percentage of completed exercises during the first follow up (after the six-week intervention) for both groups. Exercise adherence will be taken into consideration when performing the pre-protocol analysis.

All enrolled patients will be encouraged to contact the principal investigator directly if experiencing problems related to their allocated group intervention. The principal investigator will then fill out a standardized form at these calls. Patients can use medicines and nutritional products as needed, prescribed by their physician. To avoid study-contamination, patients will be asked to adhere to the allocated rehabilitation intervention and not to seek alternative health-care services during the course of the study. Patients will be advised to contact their general practitioner or the principal investigator as needed.

The physiotherapy intervention will be given to Groups A and B for six weeks. The intervention will be provided for 60 minutes, five days each week. Both Group A and Group B will receive conventional treatment. Group A will receive mCIMT along with the conventional therapy, while Group B will receive the motor relearning program along with the conventional therapy. Treatment will be provided to both groups for six weeks.

*Modified constraint-induced movement therapy (mCIMT)*

Exercises will be given to participants that have a functional focus and will be under supervision. The affected lower extremity will be the focus of these exercises. Based on the desired movements, the therapist (principal investigator) recommended these exercises.

The 30-minute mCIMT approach will consist of the following movements: Transfer package (10 minutes per session), side stepping, ball kicking, stair climbing, and knee control on a step.

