
*Motor Relearning program (MRP)*

Participants receive task-specific guidance based on the MRP. This method will be applied for 30 minutes. The actions will be practiced in both sitting and standing and should target an individual’s particular deficits: supine to side-lying to sitting, looking up at ceiling (ensure that centre of body mass does not move back when head is tilted back), without moving one’s feet, turning to gaze over each other’s shoulders and scanning the surroundings for specific items, reaching motions in multiple directions while moving the head and trunk, scooting in bed, altering the base of support (standing with your feet together, in tandem, with one foot on a step, or on one leg), squatting to pick up an object and cross over stepping.

*Conventional therapy*

Conventional therapy includes: i) Passive and active assisted range of motion exercises for upper and lower extremities; ii) stretching exercises for flexor synergy component shown in
Table 1; iii) strengthening exercises with the help of THERABAND shown in
Table 2; iv) balance training including practicing reaching beyond arm’s length while sitting and standing; and v) walking training that includes challenge to dynamic balance (
*e.g.*, obstacle courses).

**Table 1. T1:** Stretching exercises for upper extremities, pelvic position and lower extremities.

Action of the muscles	Major muscles targeted	Procedure
• Scapular retraction or hyperextension, shoulder abduction, elbow flexion, forearm supination, wrist and finger flexion • Pelvic retraction • Hip flexion, abduction, external rotation, knee flexion, ankle dorsiflexion, inversion	• Pectoralis major, Pectoralis minor, Latissimus dorsi, Biceps brachii, brachioradialis, Supinator muscle, Flexor digitorum profundas, Flexor digitorum superficialis and Palmaris longus • Piriformis and Thoracolumbar fascia • Gluteus minimus, Gluteus medius, Psoas major, Iliacus sartarius, Rectus femoris, Hamstring, Tibialis anterior	Patient position: Supine and sitting Therapist position: Standing Mode of stretching: Manual stretching, slow repetition, continuous stretch Doses: 3 repetitions with 30 seconds hold

**Table 2. T2:** Strengthening exercises for upper extremities, pelvic position and lower extremities.

Action of the muscles	Major muscles targeted	Procedure

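### Objectives 1 and 2 ask for the effect of each therapy, but the within-arm paired tests cannot separate it from conventional therapy, recovery, test practice or unblinded scoring

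*Protocol article*

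**What the plan says.** The Aims and objectives section lists three objectives:

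1. "To study the effect of mCIMT in addition to conventional therapy on balance" (BBS) and on gait (DGI).
2. "To study the effectiveness of MRP along with conventional therapy on balance (BBS) and gait (DGI) in sub-acute hemiplegic stroke".
3. "To compare mCIMT and the MRP in improving balance and gait in sub-acute hemiplegic stroke patients along with conventional therapy".

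Trial design describes the study as follows: "A single-centre, two arm, parallel group, comparative open labelled superiority trial will be conducted". Under Interventions, "Both Group A and Group B will receive conventional treatment"; mCIMT is added in Group A and MRP in Group B. Conventional therapy there includes "balance training including practicing reaching beyond arm’s length while sitting and standing", and also walking training. The Protocol subsection of Methods says that nothing is blinded. Outcomes are measured at baseline and six weeks.

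The Statistical analysis section gives two kinds of test at the 5% level. One is within-arm: "Statistical analysis will be performed for hypothesis testing for paired pre and post analysis using a paired t-test for normal data", with the Wilcoxon signed-rank test as the alternative. The other is an unpaired t-test between the groups on the change. Nothing in the article says that the pre-post results are descriptive only.

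**The concern.** The unpaired test on change answers objective 3. That leaves the paired tests for objectives 1 and 2. The protocol does not make this link in words, but no other listed analysis could serve.

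A paired test asks whether the mean change in an arm differs from zero. It does not ask why. In this trial the change in an arm can come from:

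- the added therapy;
- conventional therapy, which itself trains balance and walking, the two primary outcome domains;
- recovery over six weeks in patients enrolled in the sub-acute phase ("Sub-acute stroke in both men and women between the ages of 45 and 65 years");
- practice from repeating the tests;
- scoring by people who know that treatment has been given.

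With no conventional-only arm, nothing in the design removes the last four. A significant paired test could therefore be reported as showing that mCIMT or MRP works when the added therapy contributed nothing.

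**Working it through.** **Which analysis serves which objective**

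| Objective | Comparator needed | Present in the design? | Listed test that fits |
|---|---|---|---|
| 1. Effect of mCIMT with conventional therapy | Conventional therapy alone (add-on reading) or no treatment (package reading) | No | Paired pre-post, Group A |
| 2. Effect of MRP with conventional therapy | As above | No | Paired pre-post, Group B |
| 3. mCIMT versus MRP | The other randomised arm | Yes | Unpaired test on change |

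**The plan's own figure.** In Sample size calculation, 2 × (1.64 + 0.84)² × 4.1² / 3.7² = 2 × 6.1504 × 16.81 / 13.69 = 15.10, stated as 15 per group; adding 2 for dropout gives 17. The figure reproduces. Its difference of 3.7 (52.5 − 48.8) is a pre-post change in the mCIMT group of an earlier trial, so it too contains any background change in those patients.

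**Illustration: how often one arm's paired test is significant when the added therapy does nothing**

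Inputs from the protocol: SD before treatment 4.7, SD after 3.5, n = 15 per group, two-sided 5%.

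Assumptions, because the protocol gives neither:
- pre-post correlation r from 0.3 to 0.9;
- background gain m of 0.5, 1 or 1.85 BBS points (1.85 is half of 3.7).

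SD of change = √(4.7² + 3.5² − 2r × 4.7 × 3.5) = √(34.34 − 32.9r).

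Non-centrality = m√15 / SD of change. The probability comes from the non-central t distribution with 14 degrees of freedom and critical value 2.145.

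Example with r = 0.5 and m = 1: SD of change = √17.89 = 4.23; non-centrality = 3.873 / 4.23 = 0.92; probability 13.7%.

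| r | SD of change | m = 0.5 | m = 1 | m = 1.85 |
|---|---|---|---|---|
| 0.3 | 4.95 | 6.5% | 11.3% | 27.1% |
| 0.5 | 4.23 | 7.1% | 13.7% | 35.2% |
| 0.7 | 3.36 | 8.4% | 18.9% | 50.9% |
| 0.8 | 2.83 | 9.8% | 24.7% | 65.3% |
| 0.9 | 2.17 | 13.2% | 38.2% | 86.5% |

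With all 17 per group analysed the rates are somewhat higher: at 1 point, for example, they run from 12.3% to 42.9%.

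**The between-arm test.** If the same background gain m occurs in both arms, the expected difference in change is m − m = 0, and the test keeps its 5% level.

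**The case against.** **A softer reading of the objectives.** Objectives 1 and 2 can be read as the effect of each combined regimen rather than of the added part. Conventional therapy is then part of what is studied and no longer a confounder. This is a fair reading, and it removes one source of confounding. Recovery over time, test practice and unblinded scoring remain, so the paired test still cannot show an effect of the regimen.

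**No stated decision rule.** The protocol nowhere says that a significant pre-post change will count as proof of effect, and it calls no test confirmatory. A reader might infer that recovery will certainly be credited to the therapies, or that both will very probably be reported as effective whatever they add. The documents do not support that. They support only that the plan allows such a claim and contains nothing to prevent it. How likely it is depends on the size of the background gain, which the protocol does not give.

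**Superiority has its own test.** A reader might also infer that superiority will be judged by finding significance in one arm and not in the other. Nothing in the protocol points that way: a direct between-group test on change is planned, and the design is a superiority comparison of the two arms. A sentence ruling the practice out is only a safeguard.

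**The figures are illustrative.** This is right. With a background gain of 0.5 point the excess over 5% is small. Likewise, high power of the paired test at a true change of 3.7 would be no error in itself.

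**Conclusion.** The point holds for objectives 1 and 2 and goes no further. As designed, the trial cannot answer them as questions of effect under either reading, and the paired tests at 5% do not change that. This conclusion follows from the arms and the tests; it does not depend on the calculation.

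The calculation shows only the possible size. With zero effect of the added therapy, one arm's paired test would be significant in about 7–13%, 11–38% or 27–87% of trials for background gains of 0.5, 1 and 1.85 BBS points. These ranges rest on assumed gains and correlations, with the protocol's standard deviations and 15 patients.

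Objective 3, the trial's stated purpose of comparing the two regimens, is untouched by this defect.

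**What to change.** 1. Reword objectives 1 and 2 as describing the change from baseline under each combined regimen.
2. Report within-arm change for BBS, DGI and the secondary outcomes as mean change with a 95% confidence interval and no efficacy P-value.
3. Base every claim of effect or superiority on the between-arm comparison in objective 3, for both primary outcomes. DGI should not be dropped: objective 3 covers gait as well as balance, and this defect gives no reason to stop testing it.
4. State that within-arm P-values will not be compared to infer superiority.

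The cost is two effect claims that the design cannot support. Data, arms, visits and sample size do not change. The article gives the study status as not yet begun. Its Protocol amendments section says that further changes could not be made, but narrowing the inference alters no trial procedure and can be recorded as an amendment or as a clarification dated before analysis. A claim for either therapy over conventional therapy alone would need a conventional-only arm, which would be a different trial.

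### The between-group test is an unpaired t-test on raw change, gated by a Kolmogorov–Smirnov test; it is valid, but less precise than an analysis adjusted for the baseline score already collected

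*Protocol article*

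**What the plan says.** The Statistical analysis section of the protocol article fixes the between-group method: "an unpaired t-test will be used for two independent groups for the change in parameters readings of primary and secondary variables". A distributional check comes with it: "Data over the outcome variables will be analysed for normality (normal distribution) using Kolmogorov–Smirnov test", and "If data results over non normal distribution then alternate non parametric test will be used". The Wilcoxon signed-rank test is named for the paired pre-post analysis; the rank test that would replace the unpaired t-test is not named.

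A model appears only for another purpose: "Confounding variables will be analysed with generalised linear model to find the random and fixed effects over the outcome variables". The baseline value of the outcome is not mentioned there, and this model is not presented as the main comparison.

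Under Data collection methods, baseline outcomes are assessed before randomisation. The Protocol subsection describes simple randomisation to two groups of 17 and mentions no stratification. BBS and DGI are the primary outcomes, each defined as a change.

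The only spread figures are in Sample size calculation, for BBS: "Mean ± SD (Pre) result on BBS for mCIMT = 48.8 ± 4.7", "Mean ± SD (Post) result on BBS for mCIMT = 52.5 ± 3.5" and "Pooled std. dev. = (4.7 + 3.5)/2 = 4.1". They come from the mCIMT group of an earlier trial. No pre-post correlation and no SD of change is given.

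**The concern.** Subtracting baseline is the same as adjusting for it with a slope fixed at 1. When the true slope of the week-6 score on baseline is below 1, subtraction over-corrects. It adds avoidable noise, and it credits or penalises an arm for a chance difference at baseline. ANCOVA estimates the slope instead. In a trial of 34 patients this gains precision without recruiting anyone or measuring anything more.

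Letting a normality test decide which between-group test is run also makes the primary analysis depend on the data, when a single analysis could be fixed in advance.

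**Working it through.** **Inputs.** From Sample size calculation: BBS SD 4.7 before and 3.5 after treatment, common planning SD 4.1, difference 3.7, 15 evaluable per arm, 17 with dropout. Assumed, because the article does not give it: pre-post correlation ρ of 0.5 to 0.8, equal in both arms, with a linear relation.

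**The plan's own figure.** 2 × (1.64 + 0.84)² × 4.1² / 3.7² = 15.1, stated as 15; 15 / 0.9 = 16.7, so 17 per arm. Reproduced. The 4.1 is an average of two cross-sectional SDs, not an SD of change. With equal SDs the two coincide only at ρ = 0.5, since 2 × 4.1² × (1 − 0.5) = 4.1².

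**Variance per patient.**
- t-test on change: SDpre² + SDpost² − 2ρ·SDpre·SDpost
- ANCOVA: SDpost² × (1 − ρ²)

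Example with 4.7 and 3.5 at ρ = 0.5: change 22.09 + 12.25 − 16.45 = 17.89; ANCOVA 12.25 × 0.75 = 9.19; ratio 0.51.

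| SDs pre/post | ρ | Change | ANCOVA | Ratio | Reduction |
|---|---|---|---|---|---|
| 4.7/3.5 | 0.5 | 17.89 | 9.19 | 0.51 | 49% |
| 4.7/3.5 | 0.7 | 11.31 | 6.25 | 0.55 | 45% |
| 4.7/3.5 | 0.8 | 8.02 | 4.41 | 0.55 | 45% |
| 4.1/4.1 | 0.5 | 16.81 | 12.61 | 0.75 | 25% |
| 4.1/4.1 | 0.7 | 10.09 | 8.57 | 0.85 | 15% |
| 4.1/4.1 | 0.8 | 6.72 | 6.05 | 0.90 | 10% |

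With equal SDs the ratio reduces to (1 + ρ)/2. With 4.7/3.5 the reduction is never below 44.5% (reached near ρ = 0.745). Simulation at 15 per arm with 4.7/3.5 gave ratios of 0.45 to 0.58 for ρ from 0.3 to 0.9, with and without the 56-point ceiling.

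**Power.** 15 per arm, two-sided 5%, noncentral t. ANCOVA is charged one degree of freedom (27 instead of 28) and the factor 1 + 1/(2 × 15 − 4) = 1.038 for estimating the slope. The 3.7 is the protocol's planning difference, though it is a pre-post change within one arm; 2 points is an illustrative smaller difference.

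| SDs | ρ | 3.7 points: change → ANCOVA | 2 points: change → ANCOVA |
|---|---|---|---|
| 4.7/3.5 | 0.5 | 63.8% → 88.5% | 24.0% → 40.1% |
| 4.7/3.5 | 0.8 | 93.2% → 99.5% | 46.3% → 69.4% |
| 4.1/4.1 | 0.5 | 66.5% → 77.0% | 25.2% → 30.9% |
| 4.1/4.1 | 0.8 | 96.5% → 97.3% | 53.2% → 55.8% |

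**Shift from chance imbalance.** The slope on baseline is ρ·SDpost/SDpre: 0.37 to 0.60 with 4.7/3.5, and 0.5 to 0.8 with equal SDs. The standard error of the baseline BBS difference with 17 per arm is 4.7 × √(2/17) = 1.61 points (4.1 × √(2/17) = 1.41 with the common SD). A one-standard-error imbalance moves the change-score estimate by (1 − slope) × that amount:
- 4.7/3.5: 0.65 to 1.01 points, which is 18–27% of 3.7
- equal SDs: 0.28 to 0.70 points, which is 8–19% of 3.7

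**The normality gate.** With estimated mean and SD and uncorrected critical values, simulated Kolmogorov–Smirnov tests rejected exponential or lognormal samples in only 3–5% of cases at n = 17 and 16–25% at n = 34. As a screen it detects little.

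**The case against.** The change-score test matches the declared endpoint, and under randomisation its estimate is unbiased. That stands. A reader might infer that the plan is biased or invalid. It is not: the shift shown above exists only conditional on the imbalance observed, and it averages to zero over randomisations.

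A reader might also infer that half the information is lost on every outcome. The documents do not support this. A figure near one half depends on the post SD being smaller than the pre SD, in one arm of one earlier trial, for BBS only. With the protocol's common SD of 4.1 the loss falls to 10–25%. Nothing in the article allows a figure for DGI or the secondary outcomes.

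On the normality gate, the case for harm is weak. Simulated change scores with the 56-point ceiling were nearly normal (skewness 0.16–0.20), and the t-test kept a type I error of 5.0–5.1%, so missing such departures costs nothing. The article does not say whether a correction for estimated parameters is meant; with one, ceiling-limited post-treatment scores were flagged in about 8–11% of samples of 17. A gate that seldom fires also seldom changes the test. What remains is that it protects little and leaves the primary analysis formally dependent on the data.

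Two further readings of the modelling sentence go too far. Random effects are not ruled out, since the model is for the outcome variables and each patient has two visits. Nor does the text say that P-values will select covariates; it says only that associations will be examined. The model could contain the baseline score, but the text does not say so, and it is not the named between-group test.

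**Conclusion.** The concern holds as one of efficiency, not validity. The article commits the between-group comparison to raw change and leaves the baseline score out of it as a covariate. For BBS, at an assumed correlation of 0.5 to 0.8, ANCOVA would cut the variance by about 45–49% if the SDs 4.7 and 3.5 hold in both arms, or about 10–25% if pre and post SDs are equal at 4.1. After the small-sample charge at 15 per arm these become about 43–47% and 7–22%. The direction is the same in both cases; the size rests on the correlation and on the SD ratio, neither of which is known for this trial. For DGI and the secondary outcomes the size is unknown. The change is worth making before the study starts.

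**What to change.** Name as the primary between-group analysis, for BBS and for DGI, a linear model of the week-6 score on group and the baseline value of the same outcome. Report the adjusted difference with its 95% CI, and use the same model for each secondary outcome. Remove the Kolmogorov–Smirnov test as the gate for the between-group comparison, and fix one named rank-based analysis, such as the Wilcoxon rank-sum test on change or a rank ANCOVA, as a sensitivity analysis to be reported whatever the data look like.

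The cost is one degree of freedom and a change of wording. The baseline data are already collected, the model runs in the planned R software, and the article says that the study has yet to begin. The article also says that no further protocol changes could be carried out, so the new wording would need to go through the approving committees or into an analysis plan finalised before the data are examined.
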